## Methods

### Context

In Finland, municipalities are responsible for organizing primary health care and hospital districts for specialized medical care. Municipalities can provide primary health care services alone or jointly with other municipalities. In Jyväskylä, primary health care is delivered by the health center of Jyväskylä Cooperation Region (JYTE) for a catchment area comprising three municipalities with a total population of 140,000. Primary health care includes inpatient rehabilitation and ward care provided in health center hospitals and outpatient care in clinics at the local health care centers. The health center hospitals offer curative and rehabilitative care for patients who do not need specialist medical care. For example, after orthopedic surgery (i.e. hip or other fracture, joint replacement), performed at the Central Hospital of Central Finland, patients resident in Central Finland are transferred to their local health center hospital for inpatient care and rehabilitation, typically within the first post-operative days. The inpatient rehabilitation period ranges from a few days to a few months depending on the individual’s health status and care needs. After the inpatient period, patients are discharged to home. When needed, their independent living at home is supported through home care services provided by the social services department of their municipality of residence. The participants of this study are being recruited from the health center hospitals of JYTE.

### Design

This study is a parallel group randomized controlled trial (RCT, ISRCTN13461584) with two groups: a promotion of physical activity (ProPA, intervention) group and a standard care (control) group. Figure 1 provides an overview of the study design. Recruitment started during spring 2016 and will be finished by the end of August 2017. After the baseline measurements, participants are randomized into the two study groups. The computer-generated randomization is performed by an independent statistician. Randomization by sex, age (60 to 84 years or 85 years of age and over) and baseline gait speed (< 0.4 m/s or ≥0.4 m/s) is performed in blocks of 10 participants.

**Fig. 1 Fig1:**

RCT schedule for randomization, measurements and follow-up

All participants are measured three times at home: at baseline immediately after discharge from hospital, and at three and six months thereafter. Moreover, participants are followed up for a further six months (up to 12 months from baseline) to collect data on PA, mobility limitations, life-space mobility, fear of falling, pain and mood.

### Sample size calculation

A priori sampled size calculations are based on previously published work [20] and on our pilot study conducted among 55 community-dwelling older people who were followed up for six months after discharge from hospital. In our pilot study, using an accelerometer, daily active time measured as mean amplitude deviation (MAD) above 0.0167 g was 250 ± 103 min. It has been estimated that a 20% increase in habitual physical activity, as measured by an accelerometer, in the intervention group compared to standard care control group will be clinically meaningful [21]. For this effect size, a significance level of 0.05 for the PA outcomes and a power of 80% will be set. Thus, the required sample size is 53 participants in each group. Assuming a dropout rate of 10–15%, 60 participants per group (total 120 participants) are required.

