### Statistical analysis

All analyses will be performed using the intention-to-treat principle. Means, standard deviations and frequencies will be calculated for the demographic variables. Normality of the distributions will be tested. At baseline, the significance of differences between the intervention and control group will be tested by cross-tabulation and chi-square tests in the case of discrete variables, by Student’s t-test for independent samples for normally distributed data and by Mann-Whitney U-test for non-normally distributed continuous data. Associations between variables will be analyzed using Pearson’s correlation coefficient. The effects of the intervention will be assessed using repeated measures ANOVA, covariance analysis and linear mixed models. Generalized estimating equations (GEE) models will be used to analyze differences in changes in prevalence over three time points. The level of statistical significance will be set at *p* < 0.05 (two-sided). In all future publications, data will be reported following the criteria recommended by the CONSORT guidelines [42].

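### The stated 53 per group does not follow from the printed inputs under the planned two-sided 5% test, which needs 67 to 68; 53 matches a one-sided calculation

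*Protocol article*

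**What the plan says.** Under Sample size calculation, the article reports from its pilot that "daily active time measured as mean amplitude deviation (MAD) above 0.0167 g was 250 ± 103 min". The target is "a 20% increase in habitual physical activity, as measured by an accelerometer, in the intervention group compared to standard care control group", which the authors call clinically meaningful. The error rates follow: "a significance level of 0.05 for the PA outcomes and a power of 80% will be set". The conclusion is "Thus, the required sample size is 53 participants in each group", and after an allowance of 10–15% for dropout, "60 participants per group (total 120 participants) are required". The section says that the calculation also draws on earlier published work. It does not state whether the 0.05 is one- or two-sided, and it gives no correlation, adjusted variance or repeated-measures factor.

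Under Statistical analysis, the sidedness is fixed for the trial: "The level of statistical significance will be set at *p* < 0.05 (two-sided"). The same section lists repeated measures ANOVA, covariance analysis and linear mixed models for the intervention effect, without tying any of them to the sample size. No one-sided test is mentioned anywhere in the article.

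**The concern.** The section prints everything that a standard comparison of two means requires and presents 53 as following from it. Under the two-sided test that the article specifies, the same inputs give a clearly larger number. The gap of 14 to 15 per group is too big to come from rounding or from the choice between the normal and the t formula.

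This calculation is the only stated basis for the total of 120 participants, and it concerns the accelerometer measure that the article names as primary. If the power for the 20% target is below 80%, the chance of missing an effect that the authors consider clinically meaningful is higher than the reader is told, and a non-significant result carries less information than the stated power implies.

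**Working it through.** **Inputs**, all from Sample size calculation unless noted:
- control mean 250 min/day, SD 103 min/day
- difference 20% of 250 = 50 min/day
- standardised difference d = 50/103 = 0.4854, so d² = 0.2356
- alpha 0.05, power 80%, equal groups
- two-sided testing (Statistical analysis)
- 60 per group randomised, 10–15% dropout

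**Formula** (normal approximation): n per group = 2(z_alpha + z_power)² / d², with z_power = 0.842.

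**The plan's own figure.** With a one-sided 5% test, z_alpha = 1.645:

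n = 2(1.645 + 0.842)² / 0.2356 = 2 × 6.183 / 0.2356 = 52.5, rounded up to 53.

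This matches. The one-sided t-test gives 53.2, which strictly rounds up to 54, so the match is with the normal formula.

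**The test that the plan specifies.** With a two-sided 5% test, z_alpha = 1.960:

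n = 2(1.960 + 0.842)² / 0.2356 = 2 × 7.849 / 0.2356 = 66.6, rounded up to 67.

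The two-sided t-test gives 67.6, rounded up to 68.

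**Other two-sided readings of the printed inputs** also miss 53 (normal approximation):

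| Reading | n per group |
|---|---|
| Log scale | 75 |
| SD rising in proportion to the mean | 82 |
| 250 min taken as the intervention mean | 96 |
| Paired or one-sample | 34 |

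**Power and detectable difference**, unadjusted two-sided t-test. After dropout, 60 × 0.85 = 51 and 60 × 0.90 = 54.

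| n per group | Power for 50 min | Difference detectable with 80% power |
|---|---|---|
| 51 | 68.0% | 57.7 min (23%) |
| 53 | 69.7% | 56.6 min (23%) |
| 54 | 70.5% | 56.0 min (22%) |
| 60 | 75.1% | 53.1 min (21%) |
| 68 | 80.2% | 49.8 min (20%) |

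**What would justify 53 with a two-sided test.** Adjustment for baseline multiplies the required n by (1 − r²), where r is the correlation between baseline and follow-up. Starting from the t-test figure of 67.6, r = √(1 − n/67.6):
- n = 51: r = 0.50
- n = 53: r = 0.46 to 0.47 (0.45 from the normal figure of 66.6)
- n = 54: r = 0.45

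Without adjustment, by the normal formula, 53 would require an SD of about 92 min instead of 103, or a difference of about 56 min (22%) instead of 50. The article states none of these values.

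**The case against.** The strongest reply is that the analysis of the intervention effect is not planned as a plain comparison of means. Covariance analysis and mixed models are listed, and accelerometry is scheduled at baseline, 3 and 6 months. With a moderate baseline correlation, 53 per group could give 80% two-sided power. The section also cites published work that is not shown, and a full protocol may hold an adjusted variance that the article leaves out.

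Part of this stands. Two stronger statements are tempting, and the document does not support either.

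- **That the authors used a one-sided test, or that 53 can arise in no other way.** A reader might infer this from the numerical match, but sidedness is not stated in the sample size section, and an unstated correlation, SD or effect could also produce 53. One-sidedness is an inference.
- **That the trial's real power is 70%.** That figure belongs to an unadjusted comparison. The power of the planned models depends on a correlation that the article does not give, and could be higher.

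The reply does not remove the inconsistency. The section derives 53 from inputs that it lists, with no correlation or adjusted variance among them, and those inputs under the stated two-sided test give 67 to 68. However 53 arose, the printed inputs, test and result do not agree. Nor can a correlation of 0.45 to 0.50 be taken for granted: baseline is measured immediately after discharge, early in recovery, and may predict activity at six months only weakly.

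**Conclusion.** The concern holds as an inconsistency between the sample size paragraph and the planned test. From the printed inputs, two-sided 5% testing needs 67 (normal) or 68 (t-test) evaluable participants per group, not 53. The stated figure equals the one-sided normal-approximation result.

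For an unadjusted two-sided comparison, the power to detect 50 min/day is about 70% at 53 per group, 68 to 71% after the assumed dropout from 60, and 75% with complete retention. At 51 to 54 per group, 80% power is reached for about 56 to 58 min/day (22 to 23%), not for 50 min (20%).

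These results assume a pilot SD of 103 min in both groups, a difference of 20% of 250 min, equal group sizes and no variance reduction. Baseline adjustment would restore 80% power for 50 min only if the correlation between baseline and 6 months is at least about 0.45 to 0.50, which is an assumption.

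**What to change.** 1. Restate the sample size paragraph for the two-sided test: with 60 per group and 10–15% dropout, an unadjusted comparison has about 68 to 71% power for 50 min/day, or 80% power for about 56 to 58 min/day. Alternatively, state the baseline correlation or adjusted variance that justifies 53 two-sided, with its source.
2. Name one baseline-adjusted model, ANCOVA or a mixed model, as the primary analysis of active time. Both are already among the planned methods.
3. If 80% power for 50 min is to be claimed on the strength of that adjustment, state the assumed correlation (at least about 0.45 to 0.50). Check it against the 55-person pilot if accelerometry was repeated there; the article says that the pilot participants were followed for six months but not that the accelerometer was worn again.

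The cost is a rewritten paragraph and one analysis commitment. No participants are added, which fits a trial whose recruitment was due to end in August 2017. The price is a less favourable power statement, unless the correlation can be supported.

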### Standard care

At three months after hospital discharge, all participants are interviewed with structured questions on advice, recommendations and possible planned programs concerning the rehabilitation they received post discharge. Typically, older people receive written information on home exercises and safe walking and instructions on how to rise from a chair from a physiotherapist in the hospital ward before discharge to home. Half of the participants will have received standard care alone (control group).

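### Sixty per group does not cover the stated 10–15% dropout: at 15%, 51 remain against the 53 the plan requires

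*Protocol article*

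**What the plan says.** All the figures are in the protocol article under Sample size calculation. The evaluable number is given first: "Thus, the required sample size is 53 participants in each group". The next sentence turns it into an enrolment target: "Assuming a dropout rate of 10–15%, 60 participants per group (total 120 participants) are required". No inflation formula is given, and the text does not say which point of the 10–15% range produced 60.

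The inputs behind 53 are a pilot result ("daily active time measured as mean amplitude deviation (MAD) above 0.0167 g was 250 ± 103 min"), a target difference ("a 20% increase in habitual physical activity, as measured by an accelerometer, in the intervention group compared to standard care control group") and the error rates ("a significance level of 0.05 for the PA outcomes and a power of 80% will be set"). That section does not state whether the test is one- or two-sided. The Statistical analysis section does: "The level of statistical significance will be set at *p* < 0.05 (two-sided").

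**The concern.** The two adjacent sentences disagree. If 53 per group is what the primary comparison needs, the enrolment figure should leave at least 53 at the worst dropout the authors chose to name. Sixty does not. A trial that recruited exactly to plan, and lost exactly the proportion it expected at the upper end, would finish below its own stated requirement.

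Readers will judge the completed trial against this sample size statement, and the article commits to CONSORT reporting. The shortfall also falls on a calculation with no spare margin, because 53 itself matches a more lenient test than the one the analysis section names.

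**Working it through.** **Inputs.** From Sample size calculation: required n = 53 per group; enrolled n = 60 per group; dropout d = 10% to 15%; pilot mean 250 min, SD 103 min; 20% increase; α = 0.05; power 80%. From Statistical analysis: two-sided testing. Equal allocation follows from the equal group sizes and from the Standard care section ("Half of the participants will have received standard care alone (control group").

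**Step 1: the plan's 53.** Assume the 20% applies to the pilot mean, so δ = 0.20 × 250 = 50 min and the standardised difference is 50/103 = 0.485. With n = 2(z_α + z_β)²(SD/δ)² and (103/50)² = 4.244:

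- one-sided 0.05: 2 × (1.645 + 0.842)² × 4.244 = 52.5, so 53 (t-test solution 53.2);
- two-sided 0.05: 2 × (1.960 + 0.842)² × 4.244 = 66.6, so 67 (t-test solution 67.6, so 68).

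The 53 is therefore reproduced only one-sided. That is a separate matter. The dropout check below takes 53 as given.

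**Step 2: dropout.** Enrolment needed is n/(1 − d), rounded up. The number retained from 60 is 60(1 − d).

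| Dropout | Needed per group to keep 53 | Retained from 60 |
|---|---|---|
| 10% | 53/0.90 = 58.9 → 59 | 54 |
| 12.5% | 53/0.875 = 60.6 → 61 | 52.5 |
| 15% | 53/0.85 = 62.4 → 63 | 51 |

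Break-even dropout for 60 is 1 − 53/60 = 11.7%. The uncovered part of the range is (15 − 11.7)/(15 − 10), about two thirds.

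**Step 3: where 60 may come from.** Multiplying by (1 + d) instead of dividing by (1 − d) gives 53 × 1.125 = 59.6 at the midpoint and 53 × 1.15 = 60.95 at the upper end. Either lies close to 60, but the article shows no formula, so this is conjecture.

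**Step 4: effect on power** (t-test, standardised difference 0.485, no baseline adjustment).

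| n per group | One-sided 0.05 | Two-sided 0.05 |
|---|---|---|
| 54 (10% dropout) | 80.5% | 70.5% |
| 53 (required) | 79.9% | 69.7% |
| 51 (15% dropout) | 78.5% | 68.0% |

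The loss due to dropout alone is 79.9 − 78.5 = 1.4 points one-sided and 69.7 − 68.0 = 1.7 points two-sided. If 53 is instead assumed to give 80% two-sided power for some other effect (a standardised difference of 0.549), 51 gives 78.4%. On any of these bases the loss is about 1.5 points.

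**The case against.** The strongest reply is that this is a rounding matter. Dropout is given as an approximate range and 60 is a round number. It is sufficient at 10%, half a participant short at the midpoint and two short at the top. The uncertainty in the inputs is larger. An SD from 55 pilot participants has a relative standard error of roughly 1/√(2 × 54) = 9.6% under normality. Since n varies with SD², that is about 19% of 53, or some 10 participants per group. The text also never says explicitly that 60 holds at the 15% limit. All of this bears on how much the point matters, and it stands as a reason to call the effect small. It does not make the sentence correct: an enrolment target stated for a dropout range should hold over that range, or say where it stops holding.

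A second reply is that the analysis plan includes intention-to-treat and linear mixed models, so someone lost after the 3-month visit still contributes. That softens the loss at the analysis stage. However, the sample size section inflates 53 precisely because it counts dropouts as lost, and it claims no credit for partial data. Repeated measures ANOVA and covariance analysis are also listed, and complete cases could matter there.

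A third reply is that the 68% figure belongs mainly to the sidedness problem. That is right about its source: two-sided power is already 69.7% at 53. The dropout slip should be charged with about 1.5 points and no more.

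**Conclusion.** The concern holds. The stated enrolment of 60 per group does not deliver the plan's own 53 once dropout passes 11.7%. At the 15% the authors themselves anticipate, 51 remain, and 63 per group (126 in total, against 120) would be needed.

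The dropout arithmetic rests on nothing beyond the two printed sentences. The power figures rest on further assumptions: the 20% is applied to the pilot mean of 250 min with SD 103, and there is no gain from baseline adjustment. The article also bases its calculation on earlier published work that is not available here. Under these assumptions the isolated effect is small, about 1.5 points of power. Correcting only the dropout step would not restore 80% power for the two-sided test.

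**What to change.** Replace the enrolment sentence with one that says what 60 achieves: 60 per group retains at least 53 evaluable participants up to 11.7% dropout, and at 15% dropout 51 per group remain. Beside it, give the two-sided power for 51 to 54 per group (68% to 71% unadjusted), or the baseline-adjusted figure with the assumed correlation stated. Remove the implication that 60 suffices at 15%.

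The Design section has recruitment ending by August 2017, and the article is dated November 2017, so the change does not call for more participants. The cost is one sentence and a slightly less favourable statement of power; design, conduct and analysis are unaffected.

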### Participants and the recruitment process

Recruitment is implemented at two health center hospitals, Kyllö and Palokka, in the city of Jyväskylä, Finland. A research nurse reviews the medical records of all ambulatory and community-dwelling men and women aged 60 years and older who live in the city of Jyväskylä or its neighboring municipalities, and who have been admitted to either of the two hospitals owing to a lower limb or back musculoskeletal injury or disorder, including for limb or back surgery (e.g. hip fracture, joint replacement, aggravated arthritis), or a fall-induced injury. Patients who fulfill the inclusion criteria are then sent an information letter on the study from the research nurse. Those interested in participating have an opportunity to discuss their participation with the researcher before signing the informed consent and giving permission to review their medical records. Patients living in an institution or bedridden at the time of hospital admission, or who suffer from severe memory problems (Mini-Mental State Examination <20), alcoholism and unstable cardiovascular, pulmonary or progressive neurological disease are excluded from the study.

### Ethics

This study was approved by the ethics committee of the Health Care District of Central Finland on September 4th, 2014 (3 N/2014). Written information on the study was given to all participants. Participants signed an informed consent form prior to their participation. Proxy consent was not permitted.

### Measures

Baseline measurements start in the hospital ward and continue immediately after discharge to home. The 3- and 6-month assessments are performed in the participant’s home. Before the study start, examiners are given training in the testing procedures. At baseline, chronic conditions, use of prescription medication and the type of musculoskeletal condition that resulted in hospitalization (diagnosis) and its treatment (e.g. surgery type and medication) are drawn from the medical records of the Central Hospital of Central Finland and health center hospital. All the other measures and schedule are listed in Table 1.

**Table 1 Tab1:** Measures included in the study at each time-point

Intsrument	Domains	Time point					
		Prior to hospital admission	Baseline	3 months	6 months	12 months	Ref.
Main outcome measures							
Physical activity	Accelerometer 6 days		x	x	x	–	
	Diary of physical activity 6 days		x	x	x	–	
	Modified Grimby scale	x	x	x	x	x	[22, 23]
	YPAS (standing/walking & lying down/sitting)	x	x	x	x	x	[45]
	Unmet physical activity		x	x	x	x	[32]
Short Physical Performance Battery (SPPB)	Balance, 4 m walking, chair rising		x	x	x	–	[25]
Mobility disability	Moving outdoors	x	x	x	x	x	[46]
	Walking 500 m	x	x	x	x	x	[46]
	Walking 2 km	x	x	x	x	x	[46]
	Stair climbing	x	x	x	x	x	[46]
	Lifting (10 kg)	x	x	x	x	x	[46]
Self-rated mobility			x	x	x	x	
Secondary outcomes							
Life-Space Mobility (LSA)	Within home	x	x (modified)	x	x	x	[26]
	Outdoor	x	x (modified)	x	x	x	[26]
	Neighborhood	x	x (modified)	x	x	x	[26]
	Town	x	x (modified)	x	x	x	[26]
	Unlimited	x	x (modified)	x	x	x	[26]
Impact on Autonomy & Participation (IPA), 41 items		–	x	–	x	x	[27]
Fear of falling (FES-I), 16 items			x	x	x	x	[28]
History of falls			during preceding year	during preceding 3 months	during preceding 3 months	during preceding 6 months	
Depressive symptoms (CES-D), 20 items			x	x	x	x	[36]
Pain	Presence of musculoskeletal pain		x	x	x	x	[38]
	Pain Interference Subscale from the Brief Pain Inventory (BPI)		x	x	x	x	[29]
Maximal isometric grip strength			x			x	
Perceived environmental barriers	PENBOM		x	x^a^	x	x	[31]
	Home environment		x	x	x	x	[47]
Perceived environmental facilitators	PENFOM		x	x^a^	x	x	[31]
	Exercise facilities		x	x^a^	x	x	
	Home environment		x	x	x	x	
Barriers to physical activity	Barriers (BOPA)		x	x^a^	x	x	[30, 48]
	Avoidance of moving outdoors		x	x^a^	x	x	[48]
Health, Cognition & demographics							
Health Status	Chronic diseases, current diagnosis (needing hospital care), treatment		^b^				
Medication			^b^	x	x	x	
Self-rated health			x	x	x	x	
Cognitive impairment	Cognitive status (CERAD)		x	–	–	–	[33, 34]
	Executive functions (TMT-A & -B)		x	–	x	–	[35]
Social contacts and socioeconomic status			x	–	–	–	
Weight, height			x	–	–	–	
Unintended weight loss			x	x	x	x	
Self-rated sensory functions	Vision, hearing		x	–	–	–	[49]
Standard care & rehabilitation			x	x	x	x	[38]
Use of social and health services			x	x	x	x	[38]

^a^Using Maptionnaire

^b^confirmed by a research nurse from medical records

